### 2.11. Data Protection and Trial Management

To ensure anonymity and facilitate longitudinal data matching, a double-layer security protocol will be applied. A third-party platform, Google Forms, will be used under the PI’s license solely as a data entry interface, while the intervention will be hosted on Wix. Crucially, user registration with personal emails will not be required on Wix; access will be facilitated using generic passwords or role codes provided by the teacher.

Each student will be assigned a unique alphanumeric code to allow for traceability without revealing personal identities in the final statistical matrix. The master database containing the link between the code and the participant’s identity will be stored locally and guarded exclusively by the PI on a device with encrypted storage and protected by double-factor authentication. This master file will be destroyed once variable cross-referencing is complete. Due to the short duration and educational context of the pilot, interim analyses are not planned.

Given that the PI also teaches the subject, the analysis of the research data will be carried out strictly after the official transcripts of the participating students have been finalized and locked. This temporal separation ensures that the students’ performance in the “game” cannot bias their official grade.

Given the educational nature of the intervention, the risk of physical harm is negligible. However, specific protocols have been established to mitigate potential psychological, technical, and ethical risks. To ensure clinical and ethical safety, all narratives and clinical cases generated with the assistance of Generative Artificial Intelligence will be reviewed, corrected, and validated by the PI. This process guarantees that the content is free from gender bias, racial stereotypes, or erroneous clinical recommendations (hallucinations). To prevent potential offense or stigmatization arising from the PPDS profiles, students will be explicitly informed during the briefing that these categories are strictly playful archetypes for game mechanics and do not constitute a psychological or clinical diagnosis. In the event of persistent technical failures, the session will immediately revert to a traditional seminar format to prevent student anxiety or loss of learning time. The PI will maintain a “Field Diary” to record any spontaneous reports of student distress, technical incidents, or expressions of dissatisfaction. Any event requiring the interruption of a student’s participation will be reported to the Ethics Committee.

## 3. Expected Outcomes

As a study protocol, this article does not report empirical findings. However, based on the proposed design, the study is anticipated to generate data in the following categories:-Feasibility and implementation: The primary outcome is to establish the technical and pedagogical feasibility of integrating AI-generated narratives into the standard nursing curriculum. We expect to report completion rates, time-on-task data, and technical bottlenecks identified in the Wix platform.-Academic performance trends: Regarding the LG, the study will provide preliminary estimates of the effect size comparing the adapted (EG) versus generic (CG) methodologies. Rather than confirming statistical superiority, the data will determine if the personalized approach shows a positive trend that justifies the calculation of a larger sample size for future randomized clinical trials.-Engagement patterns: Through the exploratory analysis of the PPDS profiles, we anticipate characterizing how different personality types interact with the gamified elements. We expect to describe whether specific profiles show differential satisfaction scores compared to the standard user, providing a baseline for tailored educational strategies.-Correlation data: We expect to obtain statistical evidence regarding the relationship between student satisfaction (GAMEX scores) and academic performance, clarifying whether higher engagement correlates with actual knowledge retention in this specific demographic.

## 4. Discussion

This protocol describes a pilot intervention designed to overcome the “one-size-fits-all” limitation in current simulation-based education. Although the literature supports the efficacy of gamification, there is a lack of reproducible methods to adapt these narratives to diverse student personalities on a large scale. The significance of this study lies in its use of Generative AI to make narrative personalization feasible and sustainable for standard nursing curricula, addressing the need for cost-effective implementation strategies. If successful, this protocol could serve as a blueprint for “Precision Education” [27] demonstrating how technology can drive the next era of personalized assessment [26]. In this model, training methodologies are tailored to the psychometric profile of the learner to maximize engagement and retention.

The necessity for such an adapted approach is underscored when comparing our proposed framework with the challenges highlighted in the recent literature. For instance, while studies [17] confirm that gamification generally enhances short-term motivation, they also warn of the ‘novelty effect’, where engagement drops if the digital environment fails to sustain a meaningful connection with the learner. Generic implementations often struggle with this, as a leaderboard that motivates a competitive student might actively demoralize a collaborative one. Furthermore, most contemporary research [20] still focuses on binary comparisons (gamification versus traditional lectures). By using generic gamification as the active control group, our protocol aims to move the conversation beyond mere technological implementation toward true precision education, isolating the specific pedagogical value of psychological profiling.

The choice of a cluster-randomized design was driven by ecological validity, with the aim of testing the intervention in a real-world classroom setting rather than a controlled laboratory. However, this introduces specific risks—primarily the ethical conflict of the dual role of the Principal Investigator as both researcher and teacher. As detailed in Section 2.5 and Section 2.11, this risk is mitigated by separating the research data collection from the academic grading process and ensuring that the statistical analysis is blinded and performed by an independent co-author. Furthermore, the risk of “contamination” between groups is addressed by strictly separating the sessions and using rotating passwords for the digital platform.

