### 2.2. Study Design

A cluster-randomized, prospective, comparative, and longitudinal pilot trial with two parallel groups is proposed. The study employs a 1:1 allocation ratio (one cluster per arm) and follows a superiority framework regarding the primary hypothesis. The CG will receive a generic gamified intervention, and the EG will receive an adapted gamified intervention. The study timeline spans four consecutive weeks. Participant flow, from enrollment to close-out, follows the schedule of assessment detailed in Figure 1.

The research questions and outcome measures were developed by the teaching faculty based on curricular requirements. Students were not involved in the design, recruitment, or conduct of this study. However, results will be disseminated to participants upon completion of the academic year.

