### 2.5. Randomization and Masking

Given the nature of practical teaching (in which groups are pre-established by enrollment), simple individual randomization is not possible. Therefore, a cluster randomization design will be implemented. An independent researcher not involved in the teaching process will use (RANDOM.ORG; Randomness and Integrity Services Ltd., Dublin, Ireland) computerized random number generation software to assign the practice shifts (clusters) to either the CG or EG arm. Allocation concealment is ensured as the assignment will only be revealed to the Principal Investigator and students on the first day of the intervention.

Given the highly experiential nature of the intervention, participant blinding to the educational differences between conditions is likely only partial. However, participants will remain naive to the comparative study hypothesis and their specific allocation to either the control or experimental cohort. However, due to the logistical requirements of the intervention (the distribution of specific login codes), the Principal Investigator (PI) cannot be blinded during the sessions. To mitigate bias and ensure external control, statistical data analysis will not be performed by the PI. Instead, it will be performed by a different researcher (the co-author) who was not involved in the teaching process, using a dataset in which the group assignment is masked (coded as Group A vs. Group B).

To maintain this blinding and prevent the participants from distinguishing between the narrative formats (generic vs. adapted), the intervention relies on the physical and temporal separation of the clusters. Since Group A and Group B attend consecutive but distinct shifts, there is no simultaneous visual contact with the screens of the Control and Experimental groups. Furthermore, the clinical content and the structure of the Google Forms (Google LLC, Mountain View, CA, USA) remain visually identical for both groups; only the Wix interface ‘wrapping’ differs, and this is not visible to the other group due to the shift separation.

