### 2.7. Interventions

The intervention will be carried out in the nursing classroom of the Faculty of Health Sciences. It will be structured in four face-to-face sessions lasting 2 h each. The process will be led entirely by the PI, who will act as a teacher, clinical facilitator, and administrator of the gamified platform.

Prior to the start of the study, the digital learning environment will be developed: narrative scripts will be generated using generative AI tools. It is important to note that Generative AI is used exclusively offline during the pre-intervention design phase as a drafting tool for the narrative scripts. The AI does not interact with students in real-time, nor does it evaluate their clinical answers. All AI-generated texts are thoroughly reviewed, clinically curated, and validated by the PI prior to their integration into the Wix platform (Wix.com Ltd., Tel Aviv, Israel) to prevent any clinical hallucinations or biases. In the CG, the narrative will be linear and generic for each topic. In the EG, there will be five narrative variations per theme, adapted to the profiles of the PPDS (Tryhard, Coacher, Esthetic, Joker, and Toxic). To clarify the specific elements of adaptation and ensure reproducibility, Table 1 details the differences between the generic and adapted narratives. It is important to note that the level of clinical difficulty and the learning objectives remain invariant between groups to ensure the validity of the academic performance comparison: patient vital signs, clinical history, learning objectives, and multiple-choice questions are identical in both groups. The adaptation focuses exclusively on the narrative ‘wrapping’, the tone of the feedback, and the motivational mechanics (gamification elements) triggered by the Wix platform.

A master website will be set up on Wix. Progress will be managed through “Digital Locks”, where students will be required to solve clinical issues embedded in Google Forms. Upon submitting the correct answer, the form will return a password that will allow the student to unlock the next page (level) in Wix.

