The total cohort of 38 students will be divided into two consecutive practice shifts (Group A and Group B): one with 18 students and the other with 20. In the first session, software will be used to randomly assign which group will have the first shift. Students will remain in their assigned group for all four sessions to avoid cross-contamination. The program consists of four compulsory thematic modules:-Session 1: Prenatal care;-Session 2: Maternal-fetal assessment and well-being;-Session 3: Obstetric risk triage;-Session 4: Critical management in pregnancy.

Each day of the internship follows the same 120 min (2 h) time structure, which is visually summarized in Figure 2.

During the middle 60 min (intervention), the PI will monitor activity as the students interact with their devices. In the CG, all learners receive the same login URL and password, and the storytelling in Wix is standard. The mechanics are the same for everyone: progress bars are present, and points are awarded for correct answers. In the EG (PPDS-Adapted Gamification), at the beginning of each session, the PI provides differentiated codes (according to role) based on the learner’s profile to access five parallel narratives in Wix for the same clinical case. The clinical goal is the same for all participants, but the narrative “wrapping” and side mission change.

To ensure fidelity, the PI will be the only person with admin privileges in Wix and access to the Google Forms answers in real-time. Attendance will be monitored using signatures. The PI will resolve technical or clinical questions during the session, ensuring that the password lock in Wix does not impede the progress of learning.

Forms will be set up as “required steps” within the Wix narrative. In the case of the EG, the knowledge forms will be identical in content but esthetically matched to the identified player’s profile.

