
### 2.9. Data Collection Method

The study employs a hybrid data collection strategy to clearly separate the educational game mechanics from the research evaluation process. All formal assessments related to the study outcomes—including sociodemographic data, the PPDS, and the knowledge tests—will be administered exclusively in physical paper format. This ensures that research data collection does not depend on the stability of the digital platform during the session. Google Forms will be used solely as a functional component of the gamification (acting as “digital locks”). Participants enter their clinical answers into these forms to obtain the passwords required to advance through the Wix narrative. These digital responses serve an instructional purpose and are not the primary source for academic performance analysis.

To ensure high-quality data and minimize errors during the transition from paper to digital analysis, each student will be assigned a unique alphanumeric code on their first paper form (Form 0), which must be manually transcribed by the student onto all subsequent paper assessments (Forms 1F to 4F) to enable longitudinal matching. The PI will manually enter the data from the paper forms into a pre-configured offline database. To promote data integrity, a random 10% sample of the paper forms will be cross-checked against the digital database by a co-author to ensure transcription accuracy.

The primary strategy for participant retention is the integration of the trial into the mandatory face-to-face academic calendar. The educational value of the simulations as preparation for the final exam serves as the main incentive for completion. Reasons for any missing sessions or incomplete paper forms will be recorded in the field diary to be reported as feasibility outcomes.

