As the researcher is also the teacher who evaluates the coursework, this could introduce unconscious bias (Pygmalion Effect) to favor the EG or generate in the students a desire to please the teacher by responding positively to the surveys. To address this situation, the knowledge-assessing questionnaires contain multiple-choice questions to facilitate automatic and objective correction and eliminate subjectivity on behalf of the evaluator. Anonymity will be guaranteed for the satisfaction surveys to encourage honesty.

As for the profile self-evaluation through the PPDS, the classification of the students depends on their sincerity when answering the test. It may be that a “Toxic” student does not recognize themselves as such and marks “Coacher” answers due to social desirability, thus being assigned a narrative that does not correspond accurately to their profile. This issue will be addressed by clearly explaining that there are no “good or bad” profiles, thus reducing social pressure.

Another limiting aspect is the risk of contamination between groups. As students are classmates from the same faculty, the CG students may learn about the existence of the EG’s “special missions” and feel demotivated (demoralizing effect) or try to obtain the EG passwords. To address this issue, Wix login passwords will be changed on a per-session and group basis, and explicit confidentiality will be required as part of the “game contract”. To actively monitor this risk without increasing survey fatigue, the Principal Investigator will utilize the pre-established “field diary” to record any spontaneous student disclosures or observable evidence of cross-contamination between the shifts. Any detected contamination will be reported as a feasibility metric and factored into the interpretation of the exploratory efficacy results. While this observational approach is suitable for a pilot, future definitive trials will benefit from incorporating a formal self-report question to empirically measure cross-contamination rates.

Finally, as a logistical limitation, and given the nature of the study, failures in the faculty’s Wi-Fi connection, Wix server crashes, or problems with students’ mobile devices could interrupt the intervention. An alternative plan will be available, with changes in the teaching schedule agreed upon with the students so that a new practical session may be scheduled.

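### Separate shifts and rotating passwords do not stop test answers passing from the first shift to the second, which would bias Learning Gain by arm

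*Protocol article*

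**What the plan says.** The Discussion (Section 4) states that contamination "between groups is addressed by strictly separating the sessions and using rotating passwords for the digital platform". The Limitations (Section 4.1) describe the risk as control students learning of the experimental arm's missions, being discouraged by this, or trying to get its passwords. In response, "Wix login passwords will be changed on a per-session and group basis", and confidentiality is required under the game contract. The investigator's field diary is to note spontaneous disclosures or visible evidence of contamination. Section 2.3 makes detected cross-contamination a reason for withdrawal, and Section 2.8 lists qualitative evidence of it among the feasibility metrics.

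On timing, Section 2.7 says: "The total cohort of 38 students will be divided into two consecutive practice shifts". It adds: "In the first session, software will be used to randomly assign which group will have the first shift". Section 2.5 gives the reason for separating the shifts: "Since Group A and Group B attend consecutive but distinct shifts, there is no simultaneous visual contact with the screens". Section 2.2 fixes one cluster per arm.

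On content, Section 2.7 says that "patient vital signs, clinical history, learning objectives, and multiple-choice questions are identical in both groups". Section 2.8 describes one 40-item questionnaire, with post-tests on the same content as the initial questionnaire but altered in form and answer order. Section 2.9 puts the knowledge tests on paper and uses the online forms only as digital locks. It also says: "The educational value of the simulations as preparation for the final exam serves as the main incentive for completion".

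**The concern.** The statement in the Discussion reads as if separation and passwords deal with contamination as a whole. They act on who can see which narrative. The route that bears most directly on the primary outcome is different: a student in the first shift tells a classmate in the second shift the correct answer to a case, a lock or a test item. That needs no Wix password and no sight of a screen, and it reveals nothing about the narrative. Running the arms one after the other does not close this route. It creates the opportunity.

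Learning Gain is post-test minus pre-test. A leaked post-test answer therefore raises the second shift's gain for a reason unrelated to personalization. Section 2.10 names estimation of the effect's magnitude as the pilot's primary statistical goal, and Section 2.4 intends the estimate for the power calculation of later trials. A shift-order bias would be carried into that calculation.

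**Working it through.** **1. Does each safeguard reach test content?**

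- Password rotation governs access to Wix. The knowledge tests are on paper (Section 2.9), so it does not protect them.
- Shift separation is justified by the absence of screen contact (Section 2.5). It does not prevent conversation between shifts.
- The rewording in Section 2.8 is between pre-test and post-test. No version specific to a shift is described.
- Game-contract confidentiality is introduced as the answer to missions and passwords (Section 4.1). Its wording could cover test content but does not say so.
- The field diary and the withdrawal rule act after detection. They do not prevent leakage.

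**2. Could the analysis remove the bias?** With one cluster per arm, practice shift and arm are the same variable. The planned participant-level Mann-Whitney comparison of global Learning Gain (Section 2.10) therefore cannot separate the two. The baseline checks in the same section cannot detect leakage at post-test.

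**3. How large might it be?** The protocol gives no SD, expected score or power figure, so there is nothing to reproduce. Everything below is an assumption except the group sizes (18 and 20), the 0 to 10 scale and the averaging over four sessions.

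Assumed inputs: 10 items per session (40 divided by 4, so one item is worth one point); f, the share of the second shift informed; k, the leaked post-test items per session; q = 0.4, the chance that such an item would otherwise be missed; SD of global gain 0.75 to 1.5; no true effect; the same shift second in all four sessions.

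Expected bias = f × k × q. The last column is the share of simulated trials with Mann-Whitney p < 0.05 (18 versus 20, 4,000 runs per setting) across SDs of 0.75, 1.0 and 1.5.

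| f | k | Bias (points) | Rejection rate |
|---|---|---|---|
| 0 | 0 | 0 | 4.4% to 4.6% |
| 0.25 | 1 | 0.25 × 1 × 0.4 = 0.10 | 5.5% to 6.2% |
| 0.25 | 2 | 0.25 × 2 × 0.4 = 0.20 | 6.7% to 9.6% |
| 0.50 | 2 | 0.50 × 2 × 0.4 = 0.40 | 10.3% to 27.6% |
| 0.50 | 3 | 0.50 × 3 × 0.4 = 0.60 | 18.8% to 46.2% |

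**4. Dependence on shift order.** If one arm is second in m of the four sessions and leakage is equal in either direction, the net bias is f × k × q × (2m − 4)/4. For the 0.40 case this gives 0.40 at m = 4, 0.20 at m = 3 and 0 at m = 2. Section 2.7 describes one draw, in the first session, and no alternation. It does not say outright that the order is fixed.

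**The case against.** The strongest reply is that the safeguards are broader than the mission and password examples. Confidentiality under the game contract, the field diary, the withdrawal rule and the feasibility metric are all worded generally enough to include test content. This stands. A reader might infer that the plan protects nothing but narratives and passwords, or that its idea of contamination excludes leaked answers, and the text does not support either. What the text lacks is an explicit statement that test content is covered, and the two measures named in the Discussion do not cover it.

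The leak also rests on facts the protocol does not give. The gap between shifts is not stated. Nothing says that students are told the paper-test answers. The quoted exam-preparation incentive is not evidence that students would trade answers on a research test. A reader might also infer that leaked baseline answers would lower the second shift's gain. However, Section 2.6 describes a briefing to the whole class, and nothing says that Form 0 is given shift by shift. That branch is left out here.

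Finally, the comparison is declared exploratory, and Section 4.1 concedes confounding with cluster-level differences and lists contamination as a limitation. This limits the consequence and makes the rejection rates secondary. It does not remove the point: leakage arises during the trial, and the effect estimate is what the pilot is meant to deliver.

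**Conclusion.** The concern holds in limited form. The Discussion's statement is not correct for test content: neither session separation nor password rotation controls the passing of correct answers from the first shift to the second, and the analysis could not separate the resulting bias from the intervention effect. The bias would favour whichever arm sits second, so it could overstate or understate the effect of personalization.

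Its size cannot be derived from the protocol. Under the assumptions above it runs from about 0.1 point with light sharing, which barely moves the rejection rate, to 0.4 to 0.6 point if half the shift hears two or three of ten items. These figures assume the same order every week and would shrink if the order varied. The documents do not show that leakage will happen or that it will be large. The case for acting is that prevention is nearly free and the bias cannot be repaired afterwards.

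**What to change.** - In the Discussion and Section 4.1, state that shift separation and password rotation do not control leakage of test content.
- Extend game-contract confidentiality explicitly to test questions, lock answers and case solutions until the second shift of that week has finished.
- Record any breach as cross-contamination, both in the field diary and in the feasibility metric.

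The cost is a few sentences of text and one instruction to students. The first shift cannot discuss the session's solutions until the second shift ends. The embargo relies on students' compliance, so it reduces the risk without removing it.

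Giving the shifts different post-test versions and swapping them weekly may look attractive but is not advised. In each week it would add a test-form difference aliased with arm, and it would not stop a student passing on the correct clinical answer.
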